### Ethics Approval

This research will be carried out in compliance with the Helsinki Declaration of 1975 as revised in 2000 [26]. Personal confidentiality is guaranteed. Written informed consent forms will be collected from each participant. The consent forms emphasize the right to withdraw from the trial at any time without explanation according to the consent form template created by the Norwegian Regional Committee for Medical and Health Research Ethics (REC). Information about the trial is given orally in an information meeting as well as in written form, with the opportunity to ask questions via telephone or email.

This trial protocol has been approved by the REC (ID 15680) and is registered at ClinicalTrials.gov (NCT04000035). Possible substantial protocol modifications must be approved by the steering committee and the REC and will be registered in ClinicalTrials.gov. The participant-level data set will not be available for public access owing to General Data Protection Regulations. Metadata and statistical codes beyond those reported in publications will be available upon reasonable request.

### Statistical Analysis

#### Power Calculation

The calculation of the sample size for the number of workplaces is pragmatic and based on Odeen et al [8]. ITT sickness absence will be collected at the unit level, and a 10% reduction from 6.6% (mean certified sickness absence in Troms) to 5.9% (SD 2.5%) will be considered significant in both a clinical and societal context. Odeen et al [8] demonstrated a statistically significant 11% difference in rate ratios at the unit level, with 42 and 48 units in the 2 arms. We consider actual units for inclusion as comparable and, therefore, plan to include 50 workplaces in each arm in line with the study by Johnsen [23] on workplace interventions in kindergartens.

At the individual level, the necessary sample size to detect a clinically significant difference within the arms was calculated according to the hypothetical use of the patient activation measure. A clinically significant difference in patient activation measure between the arms can be set at *D*=5 [27]. On the basis of this, and using a quantitative method where *f*(*a*=0.05, *b*=0.20)=10.5, we can calculate the necessary sample size for the trial arms: 182 (*n* = 2[*SD*/*D*]^2^ × *f*[*a*,*b*]) individuals in each arm if the SD is 17, strength (*b*) is 80%, and significance level (*a*) is 5%. Therefore, we need to include a total of 364 participants in the trial. To take into account the lack of independence between workers in clusters, this number should be corrected by *the variance inflation factor* 1 + (*n* − 1)*ρ*, where *n* is the average cluster size and *ρ* is the intracluster correlation coefficient for the particular outcome [28]. With the value of *n* being 4, the inflation factor equals 1.3 when *P* equals .10; thus, each trial arm should include 240 individuals. This indicates that, with a 50% response rate and a mean workplace size of 20 employees, we will have the power to perform gender-stratified analyses with 50 workplaces in each study arm.

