#### Analysis of Data

Difference-in-difference analyses will be used to address any differences in sickness absence, health care refunds, and health-related quality of life between the trial arms at the unit level. Cost-effectiveness and cost-benefit analyses will compare the trial arms in terms of incremental costs based on direct and indirect costs related to interventions throughout the intervention period.

At the individual level, outcomes will be analyzed based on changes from enrollment. Moreover, 2-tailed *t* tests or Mann-Whitney *U* tests and chi-square tests will be used when appropriate. A generalized linear mixed effects Poisson model will be used to investigate possible differences in percentage of sick leave between the 2 trial arms. A multivariable, multilevel logistic, ordered logistic, and linear regression allowing for clustering at the unit level will be used according to the outcome measure (OM) analyzed. To consider changes owing to the pandemic-related temporary halt of the study, other statistical methods such as stratification will be relevant.

We will use 2-sided *P* values with *α*<.05 level of significance for all tests.

The analysis will be according to ITT regardless of protocol adherence.

Results will be reported in line with CONSORT (Consolidated Standards of Reporting Trials) guidelines.

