## Results

Inclusion began in June 2019 and was completed in July 2021, resulting in 97 included workplaces and 1383 individual consents. Recruitment of workplaces was difficult. Of the 146 recruited workplaces that had initially agreed to participate, only 97 (66.4%) finally consented to inclusion, whereof 46% (45/97) were allocated to HIW and 54% (52/97) were allocated to IWM. Reasons given for retraction were both pandemic-related and organizational challenges that would have made it difficult for the workplaces to satisfy the study requirements.

Questionnaire 1 was answered by 962 participants, yielding a response rate of 69.6% (962/1383). Although the time point for questionnaire 2 has been reached for only a part of the participants, none have received questionnaire 3 as of February 20, 2022. Data collection will be completed with the last questionnaires to be sent out in July 2023. Results on intervention-related difference-in-difference regarding self-rated health measures, sickness absence, and health care use are expected to be published from autumn 2023 onward.

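### The target effect and SD printed for unit-level sickness absence (OM 1) do not support 50 workplaces per arm: a simple comparison has about 28% power for 0.7 points

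*Protocol article*

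**What the plan says.** The Power Calculation section of the protocol article opens by conceding the basis of the size: "The calculation of the sample size for the number of workplaces is pragmatic". It says that "ITT sickness absence will be collected at the unit level" and gives the effect of interest: "a 10% reduction from 6.6% (mean certified sickness absence in Troms) to 5.9% (SD 2.5%) will be considered significant". It does not put these figures into a formula. It cites an earlier workplace trial with 42 and 48 units that found a significant 11% difference in rate ratios, and concludes: "We consider actual units for inclusion as comparable and, therefore, plan to include 50 workplaces in each arm".

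The only formal calculation in the section is at the individual level, with 80% power, for a hypothetical patient activation measure that is not among OMs 1-12.

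The Analysis of Data section plans that "Difference-in-difference analyses will be used to address any differences in sickness absence" between arms at the unit level, with two-sided tests at 0.05. The Evaluation Outcomes section defines OM 1 as the change in the workplace rate from the 24 months before allocation to months 12-24 after it. No pre-post correlation is given. The Results section reports that "46% (45/97) were allocated to HIW and 54% (52/97) were allocated to IWM".

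**The concern.** An effect, an SD and a size stand side by side under a power heading, so a reader will assume that they fit together. The Discussion strengthens that impression by calling 97 workplaces slightly below the target of 100. Yet the size comes from the fact that an earlier trial of similar size reached significance. One significant result does not establish power, and nothing is reported about that trial's variance.

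OM 1 is the only primary outcome with a target effect in the document, and it feeds the cost-benefit analysis in OM 4. If the trial has little chance of showing a 10% reduction, a non-significant OM 1 says little about whether that reduction occurred. The readers named in the article, including political decision makers, would not learn this from the section.

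**Working it through.** **Inputs**
- Difference: 6.6 − 5.9 = 0.7 percentage points as printed (0.66 if exactly 10%). Power Calculation.
- SD: 2.5 points. The text does not say whether this is the SD of workplace rates or of their change. Power Calculation.
- Size: 50 per arm planned; 45 and 52 allocated (Results).
- Test: two-sided 0.05 (Analysis of Data).
- Unit: the workplace, so no further design effect applies.
- Power of 80% as the benchmark, borrowed from the individual-level calculation because none is stated for OM 1.

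**Can 50 per arm be reproduced?** n per arm = 2 × [SD × (1.960 + 0.842) / difference]² = 2 × [2.5 × 2.802 / 0.7]² ≈ 200.2, so 201 (226 with 0.66). The printed inputs do not yield 50.

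**Power of a simple comparison** (t test), SE = SD × √(1/n₁ + 1/n₂)
- 50/50: SE = 2.5 × √0.04 = 0.50; 0.7/0.50 = 1.40; power 28.4% (25.7% for 0.66).
- 45/52: SE = 0.509; 0.7/0.509 = 1.375; power 27.5%.
- Detectable with 80% power: 1.41 points (50/50) or 1.44 points (45/52). As shares of 6.6 these are 21% and 22%.
- The 95% confidence interval at 45/52 has a half-width of about 1.0 point, so an observed difference of exactly 0.7 would not be significant.

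The same figures apply to difference-in-difference if 2.5 is already the SD of the change.

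**The precedent.** With 42 and 48 units and this protocol's difference and SD, power would be about 26%. The earlier result therefore cannot be carried over without that trial's variance.

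**If 2.5 is the SD of workplace rates.** Let r be the correlation between a workplace's pre- and post-period rates, and assume SD 2.5 in both periods. The effective SD is 2.5 × √(2(1−r)) for difference-in-difference and 2.5 × √(1−r²) for regression adjusted for the pre-period rate. At 45/52:

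| r (assumed) | Difference-in-difference power | Adjusted regression power | 80%-power difference, difference-in-difference |
|---|---|---|---|
| 0 | 16% | 27% | 2.04 |
| 0.3 | 21% | 30% | 1.70 |
| 0.5 | 28% | 35% | 1.44 |
| 0.7 | 42% | 48% | 1.12 |
| 0.8 | 58% | 62% | 0.91 |

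The last column is 1.44 × √(2(1−r)). Power reaches 80% only at r of about 0.88 (difference-in-difference) or 0.87 (adjusted).

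**Unequal SDs.** OM 1 sets a 24-month pre-period against a 12-month post-period, so the pre-period SD may be the smaller. With k = pre SD / post SD, the variance factors are 1 + k² − 2rk (difference-in-difference) and 1 − r² (adjusted). Assuming k = 0.8 and r = 0.7 they are 1 + 0.64 − 1.12 = 0.52 and 1 − 0.49 = 0.51, so the gain from adjustment almost vanishes. At r = 0.8 both are 0.36.

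**The case against.** The article calls the number of workplaces pragmatic and states no power for OM 1. A reader might infer that a power figure was miscalculated. None was, so the fault lies in the justification and not in the arithmetic.

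A reader might also infer that the 10% reduction cannot be detected. That is too strong: about 28% is low but not zero, and difference-in-difference reaches 58% at r=0.8.

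Nor is 28% the established power of the planned analysis. It holds for difference-in-difference only if 2.5 is the SD of the change, or if it is the SD of rates and r is about 0.5. A flat claim that the trial would miss its target seven times in ten treats an unstated quantity as known.

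On the model, difference-in-difference is valid under randomization and matches OM 1's definition as a change. It is tempting to say that adjustment always cuts the variance to (1+r)/2 of the difference-in-difference value, or that difference-in-difference is worse than ignoring baseline whenever r is below 0.5. Both statements need equal SDs in the two periods, which unequal period lengths make doubtful.

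Finally, inclusion closed in July 2021, no passage says that a null OM 1 would be read as no effect, and a rule for interpreting it could sit in an analysis plan that is not shown. All of this limits wording and weight. It does not make the printed effect, SD and size fit, and the low power holds over every assumed r up to 0.8.

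**Conclusion.** The point stands as an unsupported sample size. Power for 0.7 points is about 28% in a simple comparison of workplace rates, or if 2.5 is the SD of the change. The difference detectable with 80% power is about 1.4 points, roughly twice the target. If 2.5 is the SD of rates, difference-in-difference power at 45/52 runs from about 16% (r=0) to 58% (r=0.8) under equal SDs. The document offers no support for the r of about 0.88 that 80% would require. The results assume approximately normal workplace rates, equal weight per workplace and complete OM 1 data from all 97 workplaces. The estimate and confidence interval for OM 1 remain valid. What must change is what the section implies about the trial's ability to show a 10% reduction.

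**What to change.** Without enrolling more workplaces:

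1. Restate the Power Calculation section for 45 and 52 workplaces, with power for 0.7 points and the 80%-power difference over a range of r. Say whether 2.5% is the SD of rates or of change.
2. Drop the inference from the earlier trial's significance to adequate power here.
3. State that a non-significant OM 1 will be interpreted by whether its confidence interval excludes a 0.7-point reduction, and not as absence of effect.
4. Before OM 1 is analysed, make its primary model a workplace-level regression of the 12-24-month rate on arm, adjusted for the 24-month pre-allocation rate, with difference-in-difference as sensitivity analysis. Difference-in-difference fixes the pre-period coefficient at 1, whereas regression estimates it. In large samples adjustment is therefore not less precise, and the gain is modest: with equal SDs 30% against 21% power at r=0.3, 35% against 28% at r=0.5 and 62% against 58% at r=0.8. It is smaller or near zero if the pre-period SD is lower and r is high.

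No new data are needed, since eligibility already requires two years of pre-allocation absence data. The costs are a less favourable stated figure and a documented change of primary model. That change may count as a substantial modification, needing steering committee and ethics committee approval and a registry update under the Ethics Approval section.

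### The individual-level sample-size paragraph does not agree with itself on the multiplier or the cluster size, and its unconditional claim of power for gender-stratified analyses is at best marginal

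*Protocol article*

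**What the plan says.** All of the sizing text is in the protocol article, Statistical Analysis, Power Calculation, second paragraph.

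- The calculation is made "according to the hypothetical use of the patient activation measure", with D = 5 and SD = 17.
- The formula is n = 2(SD/D)² × f(a, b). The multiplier and result are printed as "0.20)=10.5, we can calculate the necessary sample size for the trial arms: 182" per arm, under the condition that "strength (*b*) is 80%, and significance level (*a*) is 5"%.
- For clustering, the result is multiplied by 1 + (n − 1)ρ, where n is defined as the average cluster size. With n "being 4, the inflation factor equals 1.3 when" the intracluster correlation is 0.10, the stated requirement becomes 240 per arm.
- The paragraph closes on this claim, made for 50 workplaces per arm: "with a 50% response rate and a mean workplace size of 20 employees, we will have the power to perform gender-stratified analyses".

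Analysis of Data specifies two-sided tests. Results reports: "Questionnaire 1 was answered by 962 participants, yielding a response rate of 69.6% (962/1383"), from 97 workplaces. The patient activation measure is not among OMs 1 to 12 in Evaluation Outcomes.

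**The concern.** A reader cannot get from the printed inputs to the printed results. The multiplier does not yield 182. The cluster size of 4 is unexplained and conflicts with the 10 respondents per workplace implied one sentence later. The inflation factor depends directly on cluster size, so the 240 per arm depends on which figure is meant.

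The paragraph then uses this calculation to assert, without conditions, that analyses by gender will be adequately powered. If that is not so, a null result in one gender could be read as evidence of no effect when the stratum was simply too small. This is also the only individual-level sizing in the article, and it rests on an instrument that is not a listed outcome. It therefore does not establish power for EQ-5D-5L or EQ VAS (OM 3, a primary outcome).

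**Working it through.** **Inputs from the protocol article:** D = 5, SD = 17, two-sided 5%, 80% power, ρ = 0.10, cluster size 4 (as used) or 20 × 0.50 = 10 (as implied), 50 workplaces per arm; 962 respondents in 97 workplaces. Normal approximation throughout.

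**1. Multiplier**

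- 2(SD/D)² = 2 × (17/5)² = 23.12.
- f at two-sided 5%, 80% power: (1.960 + 0.842)² = 7.85. Then 23.12 × 7.85 = 181.5, rounded up to 182. The plan's figure is reproduced.
- With the printed f: 23.12 × 10.5 = 242.8, rounded up to 243. It is not reproduced.
- f at two-sided 5%, 90% power: (1.960 + 1.282)² = 10.51. The printed constant is therefore the 90%-power value. One-sided values (6.18 at 80%, 8.56 at 90%) do not explain it.

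**2. Cluster inflation**

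- As printed: 1 + (4 − 1) × 0.10 = 1.3 and 182 × 1.3 = 236.6, which the plan gives as 240.
- Clusters of 4 in 50 workplaces hold only 200 people per arm, and 240 in clusters of 4 would need 60 workplaces. So 4 per cluster, 240 per arm and 50 workplaces cannot all hold.
- With the implied 10 per workplace: 1 + 9 × 0.10 = 1.9 and 182 × 1.9 = 345.8, so 346 per arm. The achieved 962/97 = 9.9 gives 1.89 and about 344.
- With 50 workplaces per arm fixed and cluster size N/50: N = 182 × [1 + (N/50 − 1) × 0.10]. So N × (1 − 0.364) = 163.8 and N = 257.5, about 258 per arm (5.2 per workplace).
- If 90% power was intended: 243 × 1.9 = 461.7, so 462 per arm in clusters of 10.

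**3. Power for the whole sample**

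Power = Φ(D / (SD × √(2/n_eff)) − 1.96), with n_eff = n / inflation factor.

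| n per arm | per workplace | factor | n_eff | power |
|---|---|---|---|---|
| 240 | 4 | 1.30 | 184.6 | 80.7% |
| 240 | 4.8 (240/50) | 1.38 | 173.9 | 78.3% |
| 240 | 10 | 1.90 | 126.3 | 64.7% |
| 500 (50 × 10) | 10 | 1.90 | 263.2 | 92.1% |

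**4. Power within a gender stratum**

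In a one-gender analysis the cluster is the same-gender respondents in a workplace. The article gives no gender split, so every split below is an assumption. Base: 500 per arm, 10 per workplace.

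| assumed split | smaller stratum per arm | per workplace | factor | needed (182 × factor) | power |
|---|---|---|---|---|---|
| 50:50 | 250 | 5 | 1.4 | 255 | 79.4% |
| 60:40 | 200 | 4 | 1.3 | 237 | 73.2% |
| 70:30 | 150 | 3 | 1.2 | 219 | 64% |

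Attrition lowers these further. If 70% of the planned respondents were analysed at 24 months (an assumption), an even split leaves 250 × 0.70 = 175 per arm in clusters of 3.5. The factor is 1.25, n_eff is 140 and power is about 69%. The Discussion itself expects lower response to questionnaires 2 and 3.

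**The case against.** **The multiplier changes no sample size.** This stands. Power of 80% and two-sided tests are both stated, and 182 is right for them. A reader might infer that the wrong constant makes 240 wrong. It does not: 10.5 is a mismatched constant unless 90% power was meant.

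**346 is not the only consistent answer.** This also stands. 346 per arm in clusters of 10 is about 35 workplaces, whereas the plan fixes 50. Spreading 182 over 50 workplaces gives 3.6 each, close to 4, so the authors may have meant required respondents per workplace; the text does not say so. On that reading 240 is only modestly low (about 258 needed, 78% power). What remains is that 4 is unexplained and conflicts with the cluster size the plan expects.

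**The gender claim is nearly met with an even split.** It is tempting to say that the plan's own inputs refute it. They do not: 250 against 255 is a shortfall of five people, well within the uncertainty of an assumed correlation of 0.10. The clear failures need an uneven split or attrition that the article does not quantify. What stands is that the claim is made without any such condition.

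**Little depends on it.** Gender-stratified analysis appears in no objective, outcome or analysis section, and inclusion is closed. This lowers the severity but does not make the paragraph correct.

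**The instrument is disclosed as hypothetical, and the reference to a difference within the arms is a slip.** Both are fair. The next sentence defines D between the arms. The disclosure means the article does not claim to have sized OM 3, but a reader should be told so plainly.

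**Conclusion.** The paragraph is internally inconsistent and should be corrected; severity is moderate.

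- The printed multiplier gives 243, not 182. Either the constant or the stated power is wrong.
- The cluster size of 4 conflicts with the plan's own 10 per workplace. In clusters of 10 the requirement is 346 per arm and 240 has about 65% power. With 50 workplaces per arm fixed, it is about 258.
- The gender-power claim is at best marginal: 79% with an exactly even split and full planned response, 73% and 64% for the smaller gender at assumed 60:40 and 70:30 splits, and less with attrition.

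A reader might conclude that the trial is underpowered at the individual level. The figures do not support that. The planned 500 per arm exceed 258, 346 and even 462, with 92% power for the unstratified comparison. All of this rests on the plan's D, SD and ρ, which belong to an instrument outside OMs 1 to 12, so none of it establishes power for OM 3 in either direction.

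**What to change.** Rewrite the paragraph as follows.

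1. Print f = 7.85 with 182 per arm at 80% power. If 90% power was intended, change the stated power and carry 243 through.
2. State the cluster size for the whole sample: 10 respondents per workplace, factor 1.9, 346 per arm, against 500 planned. If 4 was meant as something other than the expected cluster size, say what, and reconcile it with 50 workplaces per arm (about 258).
3. State the cluster size and requirement for each gender stratum. Then either withdraw the claim of gender-stratified power or give the actual power with the assumed gender split and follow-up response.
4. State that the calculation uses an instrument that is not among OMs 1 to 12 and does not establish power for OM 3.

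The cost is one paragraph of text. No participants, data collection or analyses are added, and the power stated for the gender strata becomes less favourable.

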#### Analysis of Data

Difference-in-difference analyses will be used to address any differences in sickness absence, health care refunds, and health-related quality of life between the trial arms at the unit level. Cost-effectiveness and cost-benefit analyses will compare the trial arms in terms of incremental costs based on direct and indirect costs related to interventions throughout the intervention period.

At the individual level, outcomes will be analyzed based on changes from enrollment. Moreover, 2-tailed *t* tests or Mann-Whitney *U* tests and chi-square tests will be used when appropriate. A generalized linear mixed effects Poisson model will be used to investigate possible differences in percentage of sick leave between the 2 trial arms. A multivariable, multilevel logistic, ordered logistic, and linear regression allowing for clustering at the unit level will be used according to the outcome measure (OM) analyzed. To consider changes owing to the pandemic-related temporary halt of the study, other statistical methods such as stratification will be relevant.

We will use 2-sided *P* values with *α*<.05 level of significance for all tests.

The analysis will be according to ITT regardless of protocol adherence.

Results will be reported in line with CONSORT (Consolidated Standards of Reporting Trials) guidelines.

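### Unit-level difference-in-difference for OMs 1-3 fixes the baseline slope at 1 in a randomized trial; adjusting for baseline is asymptotically never less precise and costs almost nothing

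*Protocol article*

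**What the plan says.** Under Analysis of Data, the protocol article says: "Difference-in-difference analyses will be used to address any differences in sickness absence, health care refunds, and health-related quality of life" between the arms. The sentence ends by limiting this to the unit level. It covers the first three of the four primary outcomes.

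The next paragraph turns to individuals: "At the individual level, outcomes will be analyzed based on changes from enrollment". It lists t tests or Mann-Whitney tests, says that "tests and chi-square tests will be used when appropriate", and adds two model-based analyses: "A generalized linear mixed effects Poisson model will be used to investigate possible differences in percentage of sick leave between the 2 trial arms"; and "A multivariable, multilevel logistic, ordered logistic, and linear regression allowing for clustering at the unit level will be used", chosen according to the outcome. No covariates are listed for either.

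Evaluation Outcomes defines OMs 1 and 2 as the change between the 24 months before allocation and months 12-24 after it, and OM 3 as the change from enrollment to 24 months. Adjustment for the baseline value is not mentioned anywhere in the article.

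The Results section reports 97 workplaces: "46% (45/97) were allocated to HIW and 54% (52/97) were allocated to IWM".

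**The concern.** Difference-in-difference is mainly a tool for non-randomized groups, where pre-existing level differences must be subtracted out. Here allocation is random, so any baseline difference between arms is chance, and the baseline value serves only to explain variation in the follow-up value.

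Subtracting the whole baseline value imposes a regression slope of 1. If the true slope is lower, the subtraction adds noise and over-corrects whatever imbalance arose by chance. Workplaces may have as few as 8 employees, so their absence rates will vary from period to period, and a slope close to 1 cannot be taken for granted.

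At stake are wider confidence intervals for three primary outcomes from the same data, and a between-arm estimate that depends partly on the baseline imbalance that happened to occur. Inclusion is closed, so the analysis model is one of the few places where precision can still be gained.

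**Working it through.** **Inputs from the protocol article.** Difference for OM 1: 6.6% to 5.9%, i.e. 0.7 points; SD 2.5 (Power Calculation). Planned: 50 workplaces per arm. Included: 45 and 52 (Results). Two-sided alpha 0.05.

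**Assumptions.** The article gives no pre-post correlation r and no ratio k = SD(pre)/SD(post). It does not say whether SD 2.5 describes levels or changes; it is taken here as the SD of follow-up levels. Ranges are shown for r and k.

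**The plan's own figure.** The 50 per arm is called pragmatic and has no stated power. Ignoring baseline, 80% power needs 2 × 7.85 × (2.5/0.7)² ≈ 200.2, i.e. 201 workplaces per arm. Two-sample t power, ignoring baseline, is 28% with 50 per arm and 28% with 45 vs 52.

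**Variance factors**, relative to the follow-up variance:
- difference-in-difference: 1 + k² − 2rk, which is 2(1 − r) when k = 1
- baseline-adjusted: 1 − r²
- true baseline slope: r/k

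The first minus the second is (k − r)², which is never negative and is zero only when the slope is 1. Difference-in-difference is less precise than ignoring baseline when r < k/2, i.e. below 0.5 at k = 1 and below 0.4 at k = 0.8.

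**Power for OM 1**, 45 vs 52, t test with SD 2.5 × √factor (the one degree of freedom for the slope is ignored):

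| k | r | Factors (DiD, adjusted) | Variance ratio | Power DiD | Power adjusted |
|---|---|---|---|---|---|
| 1 | 0.3 | 1.40, 0.91 | 1.54 | 21% | 30% |
| 1 | 0.5 | 1.00, 0.75 | 1.33 | 28% | 35% |
| 1 | 0.7 | 0.60, 0.51 | 1.18 | 42% | 48% |
| 0.8 | 0.3 | 1.16, 0.91 | 1.27 | 24% | 30% |
| 0.8 | 0.5 | 0.84, 0.75 | 1.12 | 32% | 35% |
| 0.8 | 0.7 | 0.52, 0.51 | 1.02 | 47% | 48% |

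At k = 1 and r = 0.9 the two are 86% and 88%.

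**Workplaces per arm for 80% power**, k = 1: difference-in-difference 281, 201 and 121 at r = 0.3, 0.5 and 0.7; baseline-adjusted 183, 151 and 103.

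**Chance imbalance.** Given the realised baseline difference, the expected difference-in-difference estimate is the true effect minus (1 − slope) × imbalance. In simulation (50 per arm, 20,000 runs, k = 1) the estimate moved by −0.50 per unit of imbalance at r = 0.5 and −0.30 at r = 0.7, against about 0 for the adjusted estimate. Averaged over all randomizations both had mean error 0.00.

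With 45 vs 52, the SE of the baseline difference at k = 1 is 2.5 × √(1/45 + 1/52) = 0.51 points. A one-SE imbalance at r = 0.5 shifts the estimate by 0.5 × 0.51 ≈ 0.25 points, 36% of the 0.7 target. At k = 0.8 and r = 0.5 the baseline SD is 2.0, the SE is 0.41 and the slope 0.625, so the shift is 0.375 × 0.41 ≈ 0.15 points.

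**The case against.** The strongest reply is that this is a choice between two valid estimators. Difference-in-difference is unbiased over randomizations, it matches an objective worded as change within and between arms, and nothing in the article contradicts it. That stands, and it makes this a point about efficiency and conditional behaviour. It is no reason to prefer the less precise estimator for the between-arm effect, since within-arm changes can be reported either way.

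Four stronger readings are tempting, and the document does not support them.

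- *The plan rules out baseline adjustment throughout.* It does not. The difference-in-difference sentence is confined to the unit level. The individual-level multilevel and Poisson models list no covariates, which an analysis plan may supply. In a linear model, change regressed on arm and baseline gives the same arm effect as follow-up regressed on arm and baseline, so analyzing changes does not exclude adjustment.
- *The 24-month baseline against a 12-month follow-up makes a slope of 1 even less suitable.* If variation is chance from period to period, the longer baseline is the steadier one. k then falls below 1 and the slope r/k moves toward 1. This shrinks the loss, as the k = 0.8 rows show.
- *All these outcomes are underpowered.* This can be shown only for OM 1. The article gives no effect size or SD for OMs 2 and 3. Its individual-level inputs (difference 5, SD 17, intracluster correlation 0.10) give about 91% power with 962 respondents.
- *Baseline adjustment rescues OM 1.* It does not: at r = 0.7 to 0.3 with k = 1 it still needs 103 to 183 workplaces per arm for 80% power.

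**Conclusion.** The point holds for the unit-level analyses of OMs 1-3. The article explicitly chooses an estimator that is asymptotically never more precise than the baseline-adjusted one and whose estimate shifts with chance imbalance whenever the true slope is below 1.

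For OM 1 the cost is about 1 to 9 percentage points of power over r = 0.3 to 0.7 and k = 0.8 to 1, and it vanishes where the slope equals 1. These sizes rest on assumed r and k and on reading SD 2.5 as the SD of levels. For OMs 2 and 3 the direction of the argument is the same, but the article gives no inputs from which to size it. For the individual-level outcomes, baseline adjustment is left unstated, which calls for clarification and is not an error.

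The change is worth making because it is nearly free, although the gain is modest.

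**What to change.** State that the between-arm effect for OMs 1-3 is estimated from the follow-up value, with arm and the baseline value as covariates: the 24-month pre-allocation value for OMs 1 and 2, and the enrollment value for OM 3. Keep difference-in-difference as a sensitivity analysis, and report within-arm changes descriptively. Add one sentence saying that the multilevel models already planned for the individual-level outcomes include the baseline value of the outcome.

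The cost is wording and one degree of freedom per model. The pre-allocation and enrollment values are already part of the planned data collection.
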